### Interventions

The esketamine treatment protocol differs for the continuous inpatient and intermittent outpatient treatment arms. The inpatient protocol is derived from a study by Sigtermans et al. [22]. For the inpatient treatment arm, esketamine is administered intravenously in CRPS patients for 6 consecutive days. Esketamine dose will be started at 0.05 mg/kg/h and can be increased to a maximum of 0.2 mg/kg/h. The dose can be increased with steps of 0.05 mg/kg/h every hour. For the outpatient treatment arm, esketamine will be administered for 6 hours. Esketamine dose will be started at 0.05 mg/kg/h and can be increased to a maximum of 0.2 mg/kg/h. The dose can be increased with steps of 0.05 mg/kg/h every hour. The increase of the esketamine dose depends on whether the patient experiences pain reduction or side effects. Once the patient notices a reduction in pain, the esketamine dose is not increased further for the duration of their admission. The investigators consider this the effective dose. If the effective dose in an earlier treatment session was higher than 0.05 mg/kg/h, the effective dose can be used as the starting dose in the following outpatient treatments.

If the patient experiences debilitating side effects the dose is reduced until the side effects disappear. Psychomimetic effects of esketamine will be treated with intravenous benzodiazepines or clonidine if necessary. In case of nausea and/or vomiting, intravenous granisetron will be administered. If the side effects subside, the esketamine dose is increased again and effects and side effects are closely monitored. If debilitating side effects persist, the esketamine therapy is discontinued. Side effects, vital parameters and pain scores will be frequently monitored by a nurse. As esketamine can induce hepatotoxicity, liver enzymes are monitored before administration and at the third day of the inpatient treatment or at the third outpatient esketamine treatment (aspartate aminotransferase (AST), alanine aminotransferase (ALT), lactate dehydrogenase (LDH), alkaline phosphatase (AF) and gamma-glutamyl transferase (GGT) [23].

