Several secondary outcome parameters will be assessed. First, sensory-discriminative dimensions of pain are assessed by using quantitative sensory testing (QST) (T0, T3) [24]. QST is a standard set of tests to characterize how somatosensory stimuli are processed and is also used to examine which types of nerve fibers might be damaged [24]. Second, information on the endogenous pain inhibitory pathway of CRPS patients will be assessed with conditioned pain modulation (T0, T3) [25]. Third, inflammatory activity will be assessed by measuring the serum level of soluble IL-2 receptor (sIL-2R) (T0, T3). sIL-2R is a surrogate marker for T-cell activation and may be used as a biomarker for monitoring T-cell involvement in CRPS-related inflammation [26, 27]. Fourth, temperature asymmetry will be measured by thermographic imaging at T0 and T3. Thermographic imaging was previously shown to be a reliable additive diagnostic tool to determine temperature differences between the affected and contralateral extremity in CRPS patients [28]. Fifth, pain intensity, syndrome severity, participation and function, emotional and physiological function, self-efficacy, catastrophizing and patient global perceived effect are assessed using the questionnaires of the core outcome measurement set for complex regional pain syndrome clinical studies (COMPACT) (T0, T2, T3, T4) [19]. The COMPACT questionnaires are defined by an international consortium of patients, clinicians and researchers as minimum core set of standardized, patient-reported questionnaires that cover important domains about the presentation and course of CRPS and factors that influence the syndrome (see Table 2) [19]. Sixth, the (effective) esketamine dose during infusion (T1). Seventh, adverse events related to esketamine treatment: dysphoria, euphoria, hallucinations, nightmares and vivid dreams, anxiety, agitation, blurry vision or diplopia, nausea or vomiting, sedation, hepatic toxicity, headache, phlebitis, infiltration/extravasation and dislodgement of peripheral intravenous catheter (T1, T2). Eight, number of administered co-interventions (benzodiazepines, clonidine, granisetron) related to adverse events (T1). Ninth, changes in the dose of pain medication during study enrolment (T0, T3, T4). Tenth, resource use and costs per patient will be assessed. Eleventh, changes in participation in employment, education or voluntary work during study enrolment (T0, T3, T4). Last, the difference in NRS pain scores over time at T1, T2, T3 and T4. The results of baseline tests or parameters will serve as a baseline and all subsequent evaluations will be compared with these results.

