### Esketamine treatment (T1A-F)

The inpatient treatment arm receives continuous intravenous esketamine infusions for 6 consecutive days during a hospital admission (T1A). The outpatient arm will receive 6 esketamine infusions: one 6-hour infusion every 2 weeks for 3 months, in a day-care setting (T1A-F). Esketamine will be administered by a trained nurse under supervision of a pain specialist.

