### Statistical methods

Descriptive statistics are used to determine the frequency distributions of demographic variables, and to describe measures of central tendency and of dispersion, dependent on the shape of their distribution. The Shapiro-Wilk test is used to analyze whether or not continuous parameters are normally distributed. The effects of the treatment on the different study parameters will be evaluated with regression models to account for the stratification factor, received esketamine treatment in the past, in the randomization process. Continuous outcomes will be analyzed with a linear regression model, where the residuals will be evaluated for normality. In case of a violation of the assumption, (logarithmic) transformations will be applied. Count outcomes will be analyzed with Poisson regression models and binary outcomes with logistic regression models. For repeated measurements mixed effects, models will be used to account for correlations from measurements within the same patient. No correction of the rejection zone will be made for multiple comparisons, because of the more explorative nature of the analyses of the secondary and other parameters. All analyses will be conducted in accordance with the intention-to-treat principle. Data will be analyzed using the latest version of SPSS and R.

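### Poisson regression is fixed for count outcomes with no allowance for variance unequal to the mean; if co-intervention counts are overdispersed, their confidence intervals will be too narrow

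*Protocol article*

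**What the plan says.** The Statistical methods section of the protocol article assigns one model family to each outcome type. For counts it says: "Count outcomes will be analyzed with Poisson regression models". The models are to be "regression models to account for the stratification factor, received esketamine treatment in the past, in the randomization process".

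For continuous outcomes the section goes further: "Continuous outcomes will be analyzed with a linear regression model, where the residuals will be evaluated for normality", with transformation if the assumption fails. It states no corresponding check or fallback for counts. For repeated data it adds: "For repeated measurements mixed effects, models will be used to account for correlations from measurements within the same patient".

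The count outcome considered here is the eighth secondary outcome in the Outcomes section: "number of administered co-interventions (benzodiazepines, clonidine, granisetron) related to adverse events (T1", where T1 is the treatment period. The Interventions section shows how these counts arise: "Psychomimetic effects of esketamine will be treated with intravenous benzodiazepines or clonidine if necessary", and granisetron is given for nausea or vomiting. Under Participant timeline, the inpatient arm has a single treatment time point (T1A) and the outpatient arm has six (T1A to T1F). No section gives a mean, variance, share of zeros or distribution for the count.

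**The concern.** Poisson regression sets the variance of the count equal to its mean, and its model-based standard errors inherit that assumption. When the true variance is larger, the point estimate remains usable, but the standard error is too small by the square root of the variance/mean ratio.

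The article gives reasons to expect patients to differ in their underlying need for co-interventions. The drugs are given in response to each patient's side effects. The infusion rate is titrated individually between 0.05 and 0.2 mg/kg/h. Treatment is stopped early if debilitating side effects persist, so exposure varies within an arm. The count also pools three agents used for different adverse events. Adjusting for prior esketamine removes only the variation that this factor explains.

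At stake is one of the tolerability comparisons that would accompany the pain result. Its confidence interval could be narrower, and its p-value smaller, than the data justify.

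**Working it through.** **Inputs.** The article gives no figure for the co-intervention count, so there is no plan figure to reproduce; its sample size calculation concerns the pain score and plays no part here. From the documents: 60 patients (Sample size) allocated 1:1 (Recruitment, allocation and blinding), hence 30 per arm. Assumed: φ = variance/mean, from 1 to 4, and mean counts of 1, 2 and 4 per patient.

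**Why φ is likely to exceed 1 for an unbounded count.** If each patient's count is Poisson around a personal rate, and rates vary between patients with coefficient of variation CV, then φ = 1 + mean × CV². Illustrations, all assumed:
- mean 2, CV 0.7: φ = 1 + 2 × 0.49 = 1.98
- mean 2, CV 1.0: φ = 1 + 2 × 1 = 3
- mean 4, CV 0.5: φ = 1 + 4 × 0.25 = 2

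**Effect on the test.** Poisson SE / true SE = 1/√φ. Real type I error of a nominal 5% test = 2 × [1 − Φ(1.96/√φ)]. For example, at φ = 2, 1.96/1.414 = 1.386, which gives 0.166.

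The formula was checked by simulation: negative binomial counts (Poisson at φ = 1), 30 per arm, no true difference, no stratum adjustment, 3,000 runs per setting. Ranges are over the three mean counts.

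| φ (assumed) | Poisson SE / true SE | Type I error, formula | Poisson, simulated | Quasi-Poisson, simulated | Robust SE, simulated |
|---|---|---|---|---|---|
| 1 | 1.00 | 5% | 4.1–4.8% | 3.6–4.8% | 4.6–5.5% |
| 1.5 | 0.82 | 11% | 10.8–11.3% | 4.7–5.2% | 5.9–6.0% |
| 2 | 0.71 | 17% | 15.8–15.9% | 4.6–5.4% | 5.5–6.9% |
| 3 | 0.58 | 26% | 24.2–25.5% | 4.4–5.2% | 5.8–7.8% |
| 4 | 0.50 | 33% | 31.2–35.1% | 5.3–6.3% | 7.0–8.5% |

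The robust column has no small-sample correction and uses the normal critical value. Its error of up to 8.5% is why the correction matters at 30 per arm.

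**If the count is the number of agents used.** For a variable X between 0 and 3 with mean m, X² ≤ 3X, so the variance is at most 3m − m² and φ ≤ 3 − m. Ratios of 3 or 4 are then impossible, and at m = 1 the ceiling is 2. If the three agents were used independently with equal probability p, then φ = 3p(1 − p)/(3p) = 1 − p, which is below 1. With p = 1/3 (assumed), φ = 0.67, the Poisson SE is 1/√0.67 = 1.22 times the true SE, and the interval is too wide.

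**The case against.** The strongest objection is that a journal article condenses the plan. Dispersion checks, scale parameters and fallback models are commonly left to the full protocol or analysis plan, neither of which is shown, and naming Poisson for counts contradicts nothing. This limits the point but does not remove it. The section does not leave the count model open: it fixes a model with a known variance restriction, and it gives a contingency for continuous outcomes only.

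A second objection is that the mixed-effects sentence already covers between-patient variation. A patient random effect would absorb it if session counts were modelled that way. That sentence is confined to repeated measurements, however, and the inpatient arm has one treatment period. For one total per patient, the natural contrast between arms, the text leaves ordinary Poisson regression.

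Several stronger readings are tempting but unsupported:
- **That the standard errors will be too small because these counts vary far more than Poisson allows.** No dispersion figure is given, so the statement can only be conditional. The definition of the count also matters: as a number of doses it is unbounded, as a number of agents it is not.
- **That the fit would give no warning.** Residual deviance or Pearson chi-square over its degrees of freedom would show the problem. The plan simply does not commit anyone to look.
- **That this is the main count outcome, or a key trade-off in the trial's decision.** It is one of twelve secondary outcomes, and the article calls those analyses explorative.
- **That unequal infusion time calls for a rate per hour.** Planned time is 6 × 24 = 144 h for inpatients, against 6 × 6 = 36 h for outpatients ("one 6-hour infusion every 2 weeks for 3 months"). Whether to compare totals or rates is a separate choice of estimand and does not follow from overdispersion.

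Explorative status does explain the absence of a multiplicity correction. It does not make a miscalibrated standard error valid.

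**Conclusion.** The point holds conditionally and is minor. The article fixes a count model that makes no allowance for variance different from the mean, for an outcome whose as-needed nature makes such a difference likely. The inflation is already material at a ratio of 1.5, where the error roughly doubles, and is absent at 1. These sizes rest on an assumed ratio, on an unbounded per-patient count and on model-based Poisson standard errors. With a 0-to-3 count, the upper part of the range cannot occur and the error may run the other way. The primary non-inferiority conclusion on pain does not depend on any of this.

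**What to change.** Replace the Poisson clause with a statement that per-patient counts will be analysed by quasi-Poisson regression, or by Poisson regression with small-sample-corrected robust standard errors, adjusted for prior esketamine treatment; negative binomial regression is an acceptable alternative. Quasi-Poisson and robust variances also handle a variance below the mean, so they serve under either reading of the count. It would help to say in the same sentence whether the count is of administrations or of distinct agents.

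The cost is one line of analysis text, with no change to treatment, data collection or sample size. Confidence intervals will usually be somewhat wider: by a factor of √φ, for example √1.5 = 1.22 or √2 = 1.41. That extra width is the uncertainty that the Poisson assumption would have hidden.

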### Recruitment, allocation and blinding

CRPS patients who are selected for a treatment with intravenous esketamine will be placed on the regular clinical waiting list of the Center for Pain Medicine. Patients will be selected chronologically from this waiting list for esketamine treatment and are contacted by a researcher for trial information. The expected duration of the study inclusion period will be approximately 3 years. The first patients will be included in 2022. Patients can withdraw from the study at any time without giving reasons. This is without any consequences for further medical treatment. Patients who are not willing to participate in this study will receive standard care (inpatient esketamine infusions).

After informed consent, patients will be enrolled and randomized using Castor software (Castor EDC). Previous treatments with esketamine may influence the outcomes of this clinical trial and therefore stratified randomization is performed with randomization blocks according to whether patients received previous esketamine treatment. The randomization will be done with an allocation ratio 1:1. The patients, researchers and statistician will not be blinded during the data collection and analysis. The researcher will enroll patients and will assign patients to the interventions after randomization.

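### The blanket intention-to-treat rule also covers outcomes that only an infusion can produce, so the comparison of adverse events, co-interventions and dose can be distorted if some patients are not treated as randomised

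*Protocol article*

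**What the plan says.** The rule is in the protocol article, Methods, Statistical methods: "All analyses will be conducted in accordance with the intention-to-treat principle". The same section assigns models by type of outcome ("Count outcomes will be analyzed with Poisson regression models and binary outcomes with logistic regression models"), which takes in event counts and yes/no events. It describes the secondary analyses as uncorrected for multiplicity "because of the more explorative nature of the analyses of the secondary and other parameters".

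Three of the secondary outcomes in the Outcomes section depend on an infusion having been given:

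- the sixth, the (effective) esketamine dose, recorded at T1;
- the seventh, introduced as "Seventh, adverse events related to esketamine treatment", recorded at T1 and T2;
- the eighth, the number of benzodiazepine, clonidine and granisetron co-interventions for adverse events, recorded at T1.

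The Participant timeline section defines T1 as the period during the esketamine treatments. Patients are randomised after consent, and Table 1 places allocation before both T0 and T1. The Recruitment, allocation and blinding section allows withdrawal at any time. The article names no separate set of patients for safety.

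**The concern.** Intention-to-treat answers what follows from being assigned to a regimen. Adverse events caused by esketamine, drugs given to counter them and the dose reached are consequences of the infusion actually received. A randomised patient who is never infused has no effective dose and cannot have an esketamine-related event, yet belongs to the as-randomised denominator. A patient who receives the other regimen has its events credited to the assigned one.

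Non-infusion is possible by design, because allocation comes before the baseline visit and the first infusion. The Background section adds that esketamine infusions have in the past been postponed or cancelled for lack of beds and staff.

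The comparison affected is one that readers will use. Scheduled infusion time is 6 × 24 = 144 hours in the inpatient arm and 6 × 6 = 36 hours in the outpatient arm. The Discussion cites the view that beyond some duration side effects may increase without added benefit. If pain relief proves non-inferior, tolerability is one of the grounds for choosing between the regimens.

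**Working it through.** The plan states no figure on this point, so there is none to reproduce. The check shows what the as-randomised rule does to a difference in event risk.

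**Inputs from the article.** 60 patients, allocated 1:1 (Sample size; Recruitment, allocation and blinding), so 30 per arm. 10% of an arm is three patients.

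**Assumed inputs, none given in the article.** Risk of at least one listed event if infused: p_I = 0.80 inpatient and p_O = 0.50 outpatient, a true difference of 30 points. Shares never infused: u_I and u_O. Shares receiving the other regimen: c_I and c_O. A never-infused patient is counted as event-free.

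**Formulas.**

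- Inpatient arm as randomised: (1 − u_I − c_I) × p_I + c_I × p_O
- Outpatient arm as randomised: (1 − u_O − c_O) × p_O + c_O × p_I

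**Non-infusion only (c_I = c_O = 0).**

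| Share never infused | Inpatients only | Both arms | Outpatients only |
|---|---|---|---|
| 0% | 80 − 50 = 30 | 30 | 30 |
| 5% | 76 − 50 = 26 | 76 − 47.5 = 28.5 | 80 − 47.5 = 32.5 |
| 10% | 72 − 50 = 22 | 72 − 45 = 27 | 80 − 45 = 35 |
| 15% | 68 − 50 = 18 | 68 − 42.5 = 25.5 | 80 − 42.5 = 37.5 |

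The change in the difference is −0.80 × u_I + 0.50 × u_O. It is zero when u_O = (0.80/0.50) × u_I = 1.6 × u_I. Below that ratio the difference shrinks; above it the difference grows.

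**Switching only (u_I = u_O = 0).** The difference is 0.30 × (1 − c_I − c_O). At 10% in one arm it is 0.30 × 0.90 = 27 points; at 10% in both arms, 0.30 × 0.80 = 24 points. Switching in either arm dilutes.

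**Other assumed risks.** With 60% and 30%, and equal shares u and c in both arms, the difference is multiplied by (1 − u − 2c). At u = c = 10% this is 0.30 × 0.70 = 21 points.

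The distortion is therefore real in principle, depends on which arm departs from plan, and vanishes when every patient is treated as randomised.

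**The case against.** The article condenses a fuller protocol, and a safety population is commonly defined in an analysis plan that is not shown. That would dispose of a complaint that a safety set is missing. It does not dispose of this point, because the article states a rule for every analysis, and a treatment-received safety set elsewhere would contradict it.

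The article does not say how a never-infused patient would be counted. Such a patient has no T1 assessment, so the values may simply be missing, and dropping missing values would give nearly the infused set anyway. This stands in part: event-free counting is an assumption of the illustration. The T2 section, however, has all patients telephoned every two weeks and asked about side effects, so a never-infused patient could have a record without events.

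A reader might infer something stronger: that patients will be counted under the wrong regimen and that a safety difference will be hidden. The documents do not support this.

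- They give no rate of non-infusion, switching or adverse events, and describe no switching between arms.
- The statement that inpatient infusion is standard care concerns patients who decline the trial. They are never randomised.
- A bed shortage that kept inpatients from being infused would also make a move from outpatient to inpatient care less likely. Combining 10% of each (72% against 53%, or 19 points) therefore joins two routes that pull against each other.
- A never-infused patient kept in the assigned arm adds to the denominator without being at risk, but is not under the wrong regimen. Only a switched patient is misattributed.
- Non-infusion confined to the lower-risk arm enlarges the difference.

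The consequence is also limited. These outcomes are secondary and exploratory. With 30 per arm and full adherence, power is about 65% for assumed risks of 60% against 30%, and 12% for 50% against 40%. Under the Monitoring section all reported or observed adverse events are recorded and serious ones followed, whatever analysis set is used.

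**Conclusion.** The point holds as a minor one. The plan fixes intention-to-treat for outcomes that require an infusion, and following that rule can distort the comparison of adverse events, co-interventions and dose between regimens.

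Neither size nor direction can be known from the documents. Under the assumed risks of 80% and 50%, with never-infused patients counted as event-free, 10% non-infusion moves a true 30-point difference to somewhere between 22 and 35 points, depending on the arm. The assumption that the inpatient regimen carries the higher risk is also not a figure from the article. The primary non-inferiority conclusion on pain does not depend on any of this.

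**What to change.** In Statistical methods, limit the intention-to-treat sentence to the efficacy, quality-of-life and cost analyses. Add that adverse events, co-interventions and esketamine dose are analysed in patients who received at least one infusion, grouped by the regimen of the first infusion received, with the as-randomised table shown as supportive. Grouping by the first infusion settles in advance where a patient with both regimens belongs. The change should be made before analysis, since the statistician is not blinded and a later choice of set would be open to question.

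The cost is a sentence or two of text, with no new data and no change to the sample size. The downside is that the safety comparison is no longer strictly as randomised, in an open trial where a change of regimen could be related to prognosis or preference; the supportive table covers this. Events in a later course of the other regimen would still be credited to the first, so any such patients should be identified in the report.
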